## Results

This study was funded by the Government of Canada’s New Frontiers in Research Fund, an operational research grant program supporting high-risk and high-reward transformative research, awarded to author RE as principal investigator in March 2019. Two extensions were provided on funding related to COVID-19 delays and parental leave of the principal investigator (RE). Author JS led a component of the feasibility trial for the purposes of her doctoral dissertation and, given the novelty of this area, analyzed data from the first 7 participants in a proof-of-concept case series format [77]. Phase 1 was completed in November 2021, and recruitment for phase 2 commenced in December 2021 and was completed in December 2023. On the basis of some of the initial challenges with recruitment, such as institutionally mandated shutdowns of clinical research, there were a few amendments to the initial protocol (Multimedia Appendix 1). The 2 major changes to the protocol were initiated because of challenges with recruitment, which were related to the COVID-19 pandemic restrictions, including university-wide research shutdowns, and changes to the formats of the Breast Health Centre’s educational sessions (classes became virtual). We opted to exclude the VR control arm for the purposes of feasibility and proceeded with a 2-armed trial (ie, VR intervention vs TAU). We also expanded recruitment to all major oncological surgeries (instead of restricting it to breast cancer surgeries) in November 2022. However, as of August 2023, no patients undergoing non–breast cancer surgery have been recruited. We conducted the first 2 focus groups in August and September 2023, and the final focus group was completed in February 2024. We will submit full feasibility results and results of the focus groups for publication after the completion of data analysis in summer 2024. After the final development of the VR program, we will apply for additional funding in winter 2024 to conduct an RCT of the final VR simulation in 2025. We will develop a separate protocol outlining the details of the final prototype and subsequent RCT.

## Discussion

### Summary

Despite the high prevalence of PSA and the significant health-related impact of PSA on perioperative outcomes, little research has examined feasible and accessible interventions. Empirically supported treatments for generalized anxiety, such as cognitive behavioral therapy, are not obtainable before surgery for most patients in Canada due to limited access to mental health professionals and limited time before surgery. To the best of our knowledge, there has not been any comprehensive immersive VR simulation to be implemented before surgery. An easily accessible simulation using VR has the potential to reduce PSA for a large number of Canadians, which may yield better postoperative health outcomes as well as cost savings to the health care system as a whole. The final novel VR intervention that we are developing is intended to be able to be used by patients independently (including in the comfort of their own homes), but it could also be offered in hospital settings (including preanesthesia clinics) and be able to be easily customized for different surgical procedures under general anesthesia. The integration of VR in health care shows tremendous growth and promise [78]. Headsets are now commercially available at low cost, and advances in the technology create growing opportunities for easy implementation (eg, stand-alone wireless VR headsets). It is expected that the release of the Apple Vision Pro, the company’s first augmented and VR headset that was unveiled in June 2023, will further increase awareness, demand, and accessibility of VR.

### Limitations

The development of this research took place during the peak of the COVID-19 pandemic, and therefore, there were unanticipated recruitment challenges and overall delays in development. First, lockdown orders initially slowed the development and refinement of the VR OR prototype itself due to work-from-home orders. Once the prototype was completed, there were further issues due to surgery delays, along with advisories against *unnecessary* hospital visits, and changes to how patients were initially approached for their interest in participating (the Breast Health Centre changed the format of education classes from in-person to virtual sessions, and eventually some classes were canceled altogether). Ultimately, from December 2021 to December 2022, only 8 participants were recruited. Of note, during this time, there were also intermittent periods where no clinical research could be conducted. However, from January to September 2023, an additional 15 participants were recruited. This increase in recruitment may relate to changes in societal and health care practices (eg, vaccinations, reduced COVID-19 hospitalizations, and the removal of public health mandates) and will be explored further in the feasibility analysis.

Although feasibility and pilot studies are critical in the development of new interventions, the generalizability of the findings is limited. Therefore, when published, the results of the feasibility trial will need to be interpreted with caution. Relatedly, the focus of these 3 initial phases has been on patients undergoing oncological surgery, namely patients undergoing breast cancer surgery, which may differ in important ways from other noncancer surgical samples. In addition, within the VR program itself, there was 1 variation of the patient avatar, and it does not reflect differences in gender, body type, or ethnicity, which may potentially decrease patient embodiment within the VR intervention and the ecological validity on the day of surgery. Furthermore, we did not ask background questions related to ethnicity, sexual orientation, or disability and, therefore, are limited in understanding feasibility aspects across diverse populations. The sample size is also underpowered to reliably detect effects but will be able to inform future RCTs in terms of design and implementation. Furthermore, preliminary trends in the data will increase confidence in the potential utility of the intervention. Relatedly, the exclusion of the VR control group (ie, non-OR VR) as per our amendment limits our ability to understand preliminary effects of the VR intervention. It is possible that any anxiety-reduction trends for the VR intervention group compared to TAU may relate to a factor other than the effect of the intervention itself (eg, an additional appointment before surgery and the opportunity to discuss fears). It will be particularly important for future RCTs to include a comparable comparison group to elucidate potential mechanisms. A future RCT is planned to test the final iteration of the VR OR, and we intend to compare it to a mobile phone–based intervention using the same components of the simulation as well as TAU. This will allow us to disentangle the potential additive effect of immersion that exists only in VR applications. Finally, recent research by our group [72] and others demonstrates that PSA for oncological surgery relates to a range of factors, including uncertainty of the health trajectory, recovery [79,80], and the psychosocial implications of surgery. Our prototype intervention only targets 1 component of PSA (ie, exposure to the OR and information regarding induction), which may not result in meaningful reductions among those with PSA related to other factors. However, the results from these 3 phases will allow us to refine the VR intervention to best meet patients’ needs and integrate all possible features to further ameliorate PSA (eg, relaxation strategies). Future versions of the simulation may also include advanced VR features, such as relevant haptic feedback, as the technology develops further.

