#### Overview

Phase 2 assessed the feasibility and preliminary outcomes of the VR OR prototype among patients undergoing breast cancer surgery. Specifically, with respect to the feasibility of this intervention, this study evaluated (1) recruitment capability and the characteristics of the resulting sample, (2) data collection procedures and selection of an appropriate outcome measure of PSA, and (3) participant acceptability and suitability of the VR OR intervention (ie, the active intervention) as well as the inclusion and acceptability of a VR control group (Nature Treks VR; ie, a non-OR immersive VR nature environment) and a TAU group. In addition, as a final aim, this study (4) pilot-tests the preliminary impact of the active intervention on PSA.

This study aimed to recruit 45 participants (n=15, 33% randomized to each arm [ie, active intervention, VR control, and TAU]). This target sample size is consistent with recommended guidelines for determining the sample size of a feasibility study and previous studies of this nature [58,59]. Furthermore, as an aim of this feasibility study, we are evaluating the extent to which we are able to recruit participants within the target population, which will inform modifications to the recruitment method as well as the expected duration of the upcoming randomized controlled trial (RCT).

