
On the day of surgery, all participants are asked to complete the PITI, the APAIS, and the NCCN Distress and Anxiety Thermometer either while they are in the waiting room or in the preoperative holding area (depending on when is most convenient and the timings of surgeries). Furthermore, we again monitor participants’ skin conductance and heart rate at this time. Participants are also asked to provide an additional rating for the NCCN Distress or Anxiety Thermometer while in the OR; instead of using the paper copy in the OR, the study coordinator or anesthesiologist asks participants to verbally indicate their current level of distress and anxiety (ie, on a scale ranging from 0 to 10). Five days after surgery, participants are asked to complete the NCCN Distress and Anxiety Thermometers; the PROMIS anxiety, depression, global health, fatigue, and pain intensity scales; a visual analog anxiety and distress graph; a postoperative summary form (to capture length of hospital stay and impressions of the various preoperative anxiety and distress measures); the BRCS; and the Peritraumatic Distress Inventory. Those in the active intervention group also receive open-ended questions requesting feedback to inform modifications that should be made to the second model of the simulation (in phase 3). Finally, 30 days after surgery, participants are asked to complete the NCCN Distress and Anxiety Thermometers; the PROMIS anxiety, depression, global health, fatigue, and pain intensity scales; the BRCS; and the Primary Care Screen for Posttraumatic Stress Disorder Diagnostic and Statistical Manual of Mental Disorders, Fifth Edition.

As will be detailed in the feasibility manuscript, although a number of self-report and objective measurements were obtained, the primary measures relate to feasibility (eg, recruitment and dropout rate as well as VR impressions and feedback). This feasibility study will also evaluate the extent to which these measures are completed as instructed and best represent PSA and whether preliminary trends support decreases in PSA across the study duration. The primary outcome measure for the larger future clinical trial will be determined based on this study. The proposed primary outcome measures of interest include the PITI, the APAIS, and the NCCN Distress and Anxiety Thermometers.

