#### Data Analysis

Quantitative data will first be analyzed descriptively: the recruitment, engagement, and attrition rates will be calculated; sample characteristics will be summarized (both across the total sample and within each group); and mean scores on measures will be reported (within each group). The assessment of acceptability will be based on open-ended qualitative feedback regarding impressions of the VR intervention, which will be analyzed using content analysis with NVivo 12 (Lumivero), which was designed to assist with qualitative data organization. We will also determine acceptability based on the developed Likert scale questions. Means or medians will be reported depending on the distribution of the data. A triangulation approach will be used to amalgamate data sources and comprehensively assess acceptability. Paired samples *t* tests (1-tailed) and repeated measures ANOVAs will assess whether there are changes in participant-reported symptoms across the duration of the study within the active intervention group. If power permits, independent samples *t* tests (or an ANOVA, followed by post hoc pairwise comparisons) will assess whether there are mean differences in PSA scores between (1) the active and control intervention groups and (2) the active intervention group and TAU (this will be examined descriptively if underpowered). We will also examine changes in physiological arousal (an objective indicator of distress), assessed via skin conductance and heart rate, between and within (ie, during VR intervention vs within OR) intervention groups, and we will assess whether self-reported distress and anxiety scores are correlated with the indices of physiological arousal. Physiological data will also be integrated in the VR technological paper (in development) to understand whether physiological indices change during the VR experience (indicative of immersion). Finally, if power permits, independent samples *t* tests and ANOVAs will assess whether there are mean differences in patient-reported symptoms according to certain sample characteristics (eg, age, clinically significant anxiety, history of previous surgery, and type of surgery), both within the active intervention group and within the complete sample.

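### An underpowered pilot commits in advance to reading undefined preliminary trends as support for utility, although the direction of a difference is weak evidence at this sample size

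*Protocol article*

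**What the plan says.** Preliminary clinical utility for preoperative state anxiety (PSA) is the secondary objective in the Abstract and the fourth aim in the Phase 2 Overview. Four parts of the protocol article bear on how it will be judged.

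- **Limitations.** The article states that "The sample size is also underpowered to reliably detect effects". The next sentence adds that "preliminary trends in the data will increase confidence in the potential utility of the intervention". The same paragraph says that "the results of the feasibility trial will need to be interpreted with caution", and that a favourable trend against TAU "may relate to a factor other than the effect of the intervention itself".
- **Measures.** The study will evaluate "whether preliminary trends support decreases in PSA across the study duration". Several candidates are listed: "The proposed primary outcome measures of interest include the PITI, the APAIS, and the NCCN Distress and Anxiety Thermometers". The primary outcome of the later trial is to be chosen on the basis of this study.
- **Data Analysis.** Change over time is tested within the active arm, with one-tailed paired t tests and repeated measures ANOVAs. The comparison of VR with TAU is tested only if power permits; otherwise "this will be examined descriptively if underpowered".
- **Overview.** "This study aimed to recruit 45 participants (n=15, 33% randomized to each arm". The target rests on feasibility guidance, not on a power calculation.

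The article does not say what counts as a trend, which measure or time point would carry the conclusion, or what an unfavourable or mixed pattern would mean.

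**The concern.** The two adjacent sentences in Limitations pull against each other. If the sample cannot reliably detect effects, the direction of an observed difference is mostly noise unless the true effect is large. Yet the second sentence commits, before results, to letting trends raise confidence, and it names no pattern that would lower it. Since the article itself concedes low power, the descriptive fallback in Data Analysis is the likely route for VR against TAU. What remains as evidence for a stated objective is then an undefined trend, readable on several scores.

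The Results section says that funding for a randomized trial will be sought after this work. A statement that trends supported utility could enter that case while carrying little information.

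**Working it through.** **Inputs from the protocol article**

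- Target size: 45 in three arms, 45 / 3 = 15 per arm (Overview). This is the only design figure on this point, and its arithmetic holds. No power, alpha, effect size or SD accompanies it.
- Arms in use: the VR control arm was dropped, leaving VR against TAU (Results).
- Recruitment: 8 by December 2022 and 15 more by September 2023, so 8 + 15 = 23 (Limitations). Recruitment ran on to December 2023, and the final number is not given.
- Candidate scores: PITI, APAIS, Distress Thermometer and Anxiety Thermometer. That is four, or three if the thermometers count as one instrument (Measures).

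**Assumptions, not in the article**

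- A common correlation ρ between the measures, shown from 0.3 to 0.9.
- Approximately normal mean differences.
- For the smaller sample, 23 people split evenly (11.5 per arm).
- True effects of 0.5 SD benefit and 0.2 SD harm, as illustrations.

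**Step 1. One measure, no effect.** The estimated difference is symmetric about zero, so it favours VR with probability 0.50 at any sample size.

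**Step 2. Any of k measures, no effect.** With φ and Φ the standard normal density and distribution function,

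P(at least one favours VR) = 1 − ∫ φ(x) · Φ(−√ρ·x / √(1−ρ))^k dx.

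| ρ | k = 4 | k = 3 |
|---|---|---|
| 0.3 | 86.0% | 80.2% |
| 0.5 | 80.0% | 75.0% |
| 0.7 | 72.9% | 69.0% |
| 0.9 | 63.1% | 60.8% |

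Two checks for k = 4: independence gives 1 − 0.5⁴ = 93.8%, and ρ = 0.5 has the exact value 1 − 1/5 = 80%.

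**Step 3. How well direction separates benefit from no effect.** A true benefit of d SD shifts the standardized difference by d·√(n/2). For d = 0.5 and n = 15 this is 0.5 × √7.5 = 1.37.

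| Reading of a trend | Benefit 0.5 SD | No effect | Ratio |
|---|---|---|---|
| One named measure favourable | 91.5% | 50% | 1.8 |
| Any of four, ρ = 0.3 | 99.8% | 86.0% | 1.2 |
| Any of four, ρ = 0.9 | 95.9% | 63.1% | 1.5 |
| All four, ρ = 0.5 | 77.3% | 20.0% | 3.9 |

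With a true harm of 0.2 SD, one measure still favours VR with probability Φ(−0.2 × √7.5) = Φ(−0.55) = 29%.

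**Step 4. Precision of VR minus TAU.** The 95% half-width in SD units is t(0.975, 2n−2) × √(2/n).

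- n = 15: 2.048 × 0.365 = 0.75 SD.
- n = 11.5: 2.080 × 0.417 = 0.87 SD.

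An observed benefit of 0.30 SD at 15 per arm would thus have an interval from 0.30 − 0.75 = −0.45 to 0.30 + 0.75 = 1.05 SD, where negative values mean harm.

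**Step 5. Scope.** Steps 1 to 4 concern the difference between arms only. The decreases over time raised in Measures are tested within the active arm. No chance figure is computed for those, but they have no comparator, and the introduction describes PSA as transient and tied to the upcoming stressor. Change unrelated to VR could therefore produce a decrease.

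**The case against.** The strongest reply is that the article contains no decision rule to attack. A reader might infer from the open list of measures that a favourable sign on any one of four scores will count as support. The document does not say so: the sentence is a loose remark in a Limitations section, and the planned analysis includes group means and formal tests. This stands. The 63% to 86% range describes the most permissive reading and rests on assumed correlations. A reader might also infer that trends cannot distinguish a useful intervention from a useless one. That goes too far: the ratios in Step 3 are all above 1, and requiring agreement across all four measures does noticeably better.

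It can also be said that the article already urges caution, that its primary measures concern feasibility, and that the later trial is not made conditional on any trend. These points limit the consequence but do not remove it. The call for caution follows from limited generalizability, and the remark on other causes concerns attribution, such as an extra appointment. Neither says that a favourable direction may be chance. Only the admission of low power does, and the next sentence undercuts it.

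Finally, the question in Measures is neutral, since it asks whether trends support a decrease, and description when power is lacking is ordinary pilot practice. Both points stand, and neither text needs to be deleted.

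**Conclusion.** The point holds in a limited form. The fault is the unconditional advance inference in Limitations, set beside an admission that the sample cannot support it. Under no effect, even one measure named in advance would favour VR half the time; accepting any of four would raise that to about 63% to 86%, given correlations of 0.9 to 0.3. With a half-width of about 0.75 SD at 15 per arm, or about 0.87 SD if 23 people were split evenly, a favourable direction does not exclude no effect or harm. The 50% needs only symmetry of the estimated difference about zero under no effect. The other figures rest on the listed assumptions and apply only to VR against TAU.

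**What to change.** Replace the sentence in Limitations with, for example:

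> The direction of a difference, or a decrease within the VR arm alone, will not be taken as evidence of utility. VR minus TAU differences on the day of surgery will be reported with 95% confidence intervals for all candidate PSA measures together, whatever their direction, and used only to describe which effect sizes remain plausible for the RCT.

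Keep the neutral question in Measures. Do not add a requirement that the interval exclude no benefit: that would be a significance test in a pilot with about 26% two-sided power at the 5% level for 0.5 SD at 15 per arm, so a useful intervention would fail it roughly three times in four.

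The change is to wording and reporting only and needs no new data, since all candidate measures are already collected on the day of surgery. The cost is that the feasibility paper will probably have to call utility undetermined.

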
### Conclusions

We are developing, testing, and refining a novel VR intervention aimed to reduce PSA before major oncological surgery using a general anesthetic. The development of the VR simulation is guided by both experts in the field and people with lived experience. VR is a promising tool, given its ability to be broadly disseminated. This study will lay the groundwork for a promising intervention to reduce PSA before major oncological surgery, and future iterations could be easily adapted to other forms of surgery. This ultimately may have significant positive effects on patient health postoperative outcomes and patient experience, along with cost savings for health care systems in the future.

## Appendix

Multimedia Appendix 1 Virtual reality study ethics amendment submission details.

## Abbreviations

APAIS: Amsterdam Preoperative Anxiety Information Scale
BRCS: Brief Resilient Coping Scale
HSC: Health Sciences Centre
NCCN: National Comprehensive Cancer Network
OR: operating room
PITI: Preoperative Intrusive Thoughts Inventory
PROMIS: Patient-Reported Outcomes Measurement Information System
PSA: preoperative state anxiety
RCT: randomized controlled trial
TAU: treatment as usual
VR: virtual reality
VR-CORE: Virtual Reality Clinical Outcomes Research Experts
